## **10 ETHICAL CONSIDERATIONS**

### **10.1 Regulation statement**

This trial will be conducted in accordance with the current ICH-GCP Guidelines.

Good clinical practice (GCP) is an international ethical and scientific quality standard for designing, conducting, recording, and reporting trials that involve the participation of human subjects. Compliance with these standard provides public assurance that the rights, safety and well being of trial subjects are protected, consistent with the principles that have their origin in the Declaration of Helsinki, and that the clinical trial data are credible.

### **10.2 Recruitment and consent**

Prior to entry in the study, the investigator or a person designated by the investigator must explain to potential subjects or their legally acceptable representative the study and the implications of participation. Subjects will be informed that their participation is voluntary and that they may withdraw from the trial at any time. They will be informed that choosing not to participate or to withdraw from the trial will not have an impact on the care the subject will receive for the treatment of his/her disease. Finally, they will be told that their records may be accessed by the IEC/IRB, regulatory authorities and authorized representatives of the sponsor without violating the confidentiality of the subject, to the extent permitted by the applicable laws and or regulations. By signing the ICF, the subject is authorizing such access.

In case the subject is unable to read and write, an impartial witness must confirm the informed consent.

The subject will be given sufficient time to read the ICF and to ask additional questions. After this explanation and before entry in the trial, consent should be appropriately recorded by means of the subject's personally dated signature or by the signature of an independent witness who certifies the subject's consent in writing. After having obtained the consent, a copy or the signed and dated informed consent must be given to the subject.

Any information relevant to the subject's willingness to participate in the study will be provided to the subject in a timely manner by means of updated ICF. This amended ICF will be signed and dated by the subject and the investigator to document the willingness of the subject to continue with the trial.

This signed and dated amended version will be filled together with initial signed and dated ICF.

### 10.3 Compensation for injury

The sponsor/investigator has a liability insurance which is in accordance with article 7, subsection 6 of the WMO.

The sponsor (AMR) has an insurance which is in accordance with the legal requirements in the Netherlands (Article 7 WMO and the Measure regarding Compulsory Insurance for Clinical Research in Humans of 23th June 2003). This insurance provides cover for damage to research subjects through injury or death caused by the study.

1. € 450.000,-- (i.e. four hundred and fifty thousand Euro) for death or injury for each subject who participates in the Research;
2. € 3.500.000,-- (i.e. three million five hundred thousand Euro) for death or injury for all subjects who participate in the Research;
3. € 5.000.000,-- (i.e. five million Euro) for the total damage incurred by the organisation for all damage disclosed by scientific research for the Sponsor as 'verrichter' in the meaning of said Act in each year of insurance coverage.

The insurance applies to the damage that becomes apparent during the study or within 4 years after the end of the study.

For subject's participating in this study insurance is covered by the AMR (Academisch Medisch Centrum Medical Research)

### 10.4 Incentives

Except for travelling expenses no special compensation or incentives will be applicable to participating subjects.

## **11. ADMINISTRATIVE ASPECTS AND PUBLICATION**

### **11.1 Handling and storage of data and documents**

Storage of all study information will be carried out by a database. The outline for this database needs to be specially suited and designed for HBV patients. A person designated by the investigator concerning the development of this database will be applied and will take care of processing this information. Human materials (PBMC's) will be kept in a -80°C freezer until ready for processing. Information concerning this study will only be available by the study investigator and the designated people by the use of passwords.

### **11.2 Amendments**

Amendments are changes made to the research after a favourable opinion by the accredited METC has been given. All amendments will be notified to the METC that gave a favourable opinion.

### **11.3 Annual progress report**

The investigator will submit a summary of the progress of the trial to the accredited METC once a year. Information will be provided on the date of inclusion of the first subject, numbers of subjects included and numbers of subjects that have completed the trial, serious adverse events/ serious adverse reactions, other problems, and amendments.

### **11.4 End of study report**

The investigator will notify the accredited METC of the end of the study within a period of 8 weeks. The end of the study is defined as the last patient's last visit.

In case the study is ended prematurely, the investigator will notify the accredited METC, including the reasons for the premature termination.

Within one year after the end of the study (end of short term follow-up after 72 weeks), the investigator/sponsor will submit a final study report with the results of the study, including any publications/abstracts of the study, to the accredited METC.

### **11.5 Public disclosure and publication policy**

After interim analysis and yearly during long term follow up (5 years) the results of this study will be presented and published.

In accordance with generally recognized principles of scientific collaboration, co-authorship with any company personnel will be discussed and mutually agreed upon before submission of a manuscript to a publisher.

## 13. APPENDIX

Figure 1. Natural history of chronic HBV infection

[figure not shown]

## Schedule of Assessments

Table 1. Schedule of Assesments

| Assessment/ Procedure                                   | Screening
(weeks) | Study treatment Period Peg-INF and ADF, Peg-IFN and tenofovir or no treatment
(weeks) |       |   |   |   |   |   |    |    |    |    |    |    |    | Follow-up
(weeks) |   |   |    |    |    |    |
|---------------------------------------------------------|----------------------|------------------------------------------------------------------------------------------|-------|---|---|---|---|---|----|----|----|----|----|----|----|----------------------|---|---|----|----|----|----|
|                                                         |                      | B                                                                                        | Day 3 | 1 | 2 | 4 | 6 | 8 | 12 | 18 | 24 | 30 | 36 | 42 | 48 | 2                    | 4 | 8 | 12 | 16 | 20 | 24 |
| Study weeks                                             | -4 to 0              |                                                                                          |       |   |   |   |   |   |    |    |    |    |    |    |    |                      |   |   |    |    |    |    |
| Informed consent, medical history                       | X                    |                                                                                          |       |   |   |   |   |   |    |    |    |    |    |    |    |                      |   |   |    |    |    |    |
| Physical examination                                    | X                    | X                                                                                        |       | X | X | X |   | X | X  |    | X  |    | X  |    | X  |                      | X |   | X  |    |    | X  |
| Liver biopsy (preceding 12 months)                      | X                    |                                                                                          |       |   |   |   |   |   |    |    |    |    |    |    | X  |                      |   |   |    |    |    |    |
| Urine or serum pregnancy test a              |                      | X                                                                                        |       |   |   | X |   | X | X  | X  | X  | X  | X  | X  | X  |                      | X | X | X  | X  | X  | X  |
| Chest X-ray, selected patients b             | X                    |                                                                                          |       |   |   |   |   |   |    |    |    |    |    |    |    |                      |   |   |    |    |    |    |
| Ultrasound of the liver                                 | X                    |                                                                                          |       |   |   |   |   |   |    |    |    |    |    |    | —  |                      |   |   |    |    |    |    |
| Fibroscan                                               | X                    |                                                                                          |       |   |   |   |   |   |    |    |    |    |    |    | X  |                      |   |   |    |    |    |    |
| CT or MRI, selected patients c               |                      |                                                                                          |       |   |   |   |   |   |    |    |    |    |    |    |    |                      |   |   |    |    |    |    |
| Electrocardiogram, selected patients d       | X                    |                                                                                          |       |   |   |   |   |   |    |    |    |    |    |    |    |                      |   |   |    |    |    |    |
| Anti-HAV IgM, anti-HIV, anti-HCV,
HCV-RNA, anti-HDV  | X                    |                                                                                          |       |   |   |   |   |   |    |    |    |    |    |    |    |                      |   |   |    |    |    |    |
| Ophthalmologic examination e (on indication) | X                    |                                                                                          |       |   |   |   |   |   |    |    |    |    |    |    |    |                      |   |   |    |    |    |    |

| Assessment/ Procedure                                                                                                                                     | Long term Follow-up
(years) |   |   |   |   |
|-----------------------------------------------------------------------------------------------------------------------------------------------------------|--------------------------------|---|---|---|---|
|                                                                                                                                                           | 1                              | 2 | 3 | 4 | 5 |
| Years                                                                                                                                                     |                                |   |   |   |   |
| Physical examination                                                                                                                                      | X                              | X | X | X | X |
| Complete hematology with differential WBC, and platelets g
(on indication)                                                                  |                                |   |   |   |   |
| Chemistry 1 g                                                                                                                                  | X                              | X | X | X | X |
| Chemistry 2 g (on indication)                                                                                                                  |                                |   |   |   |   |
| Chemistry 3 (on indication)                                                                                                                               |                                |   |   |   |   |
| Fibroscan f                                                                                                                                    | X                              |   | X |   | X |
| HBeAg, anti-HBe (frozen for central processing)HBV-DNA
(frozen for central processing) h HBsAg, anti-HBs (frozen for
central processing) | X                              | X | X | X | X |
| Ultrasound, CT or MRI (on indication) c                                                                                                                   |                                |   |   |   |   |
| PBMC's (frozen for central processing)                                                                                                                    | X                              | X | X | X | X |
| Paxgene TM RNA (k)                                                                                                                             | X                              | X | X | X | X |
| Plasmatube (proteomics profiling) (l)                                                                                                          | X                              | X | X | X | X |
| Quality of life (m)                                                                                                                            | X                              | X | X | X | X |

Table 2 (cont.) Schedule of Assessments

| Assessment / Procedure                                                           | Screening
(weeks) | Study treatment Period
(weeks) |       |   |   |   |   |   |    |    |    |    |    |    |                 | Follow-up
(week) |                 |                 |                 |    |    |                 |
|----------------------------------------------------------------------------------|----------------------|-----------------------------------|-------|---|---|---|---|---|----|----|----|----|----|----|-----------------|---------------------|-----------------|-----------------|-----------------|----|----|-----------------|
|                                                                                  |                      | B                                 | day 3 | 1 | 2 | 4 | 6 | 8 | 12 | 18 | 24 | 30 | 36 | 42 | 48 a | 50 a     | 52 a | 56 a | 60 a | 64 | 68 | 72 a |
| Study weeks                                                                      | -4 to 0              |                                   |       |   |   |   |   |   |    |    |    |    |    |    |                 |                     |                 |                 |                 |    |    |                 |
| Complete hematology with differential WBC, and platelets g            | X                    | X                                 | X     | X | X | X | X | X | X  | X  | X  | X  | X  | X  | X               | X                   | X               | X               | X               |    |    | X               |
| Chemistry 1 g                                                         | X                    | X                                 |       |   |   | X |   | X | X  | X  | X  | X  | X  | X  | X               | X                   | X               | X               | X               | X  | X  | X               |
| Chemistry 2 g                                                         | X                    | X                                 |       |   |   | X |   |   | X  |    | X  |    | X  |    | X               |                     |                 |                 | X               |    |    | X               |
| Chemistry 3                                                                      | X                    |                                   |       |   |   |   |   |   |    |    |    |    |    |    | X               |                     |                 |                 |                 |    |    | X               |
| Urinalysis, dipstick (on indication) g                                | X                    | X                                 |       |   |   | X |   | X | X  |    | X  |    | X  |    | X               |                     | X               |                 | X               |    |    | X               |
| Ceruloplasmin, alfa-1-antitrypsin                                                | X                    |                                   |       |   |   |   |   |   |    |    |    |    |    |    |                 |                     |                 |                 |                 |    |    |                 |
| Alfa-fetoprotein                                                                 | X                    |                                   |       |   |   |   |   |   |    |    | X  |    |    |    | X               |                     |                 |                 |                 |    |    | X               |
| AMA, ANA, ASMA, thyroid peroxidase antibodies,
selected patients h | X                    |                                   |       |   |   |   |   |   |    |    |    |    |    |    | X               |                     |                 |                 |                 |    |    |                 |
| HBeAg, anti-HBe (frozen for central processing)                                  | X                    | X                                 |       |   |   |   |   |   |    |    |    |    |    |    | X               |                     |                 |                 |                 |    |    |                 |
| HBsAg, anti-HBs (frozen for central processing)                                  | X                    | X                                 | X     | X | X | X | X | X | X  | X  | X  | X  | X  | X  | X               | X                   | X               | X               | X               | X  | X  | X               |
| HBV-DNA (frozen for central processing) i                             | X                    | X                                 | X     | X | X | X | X | X | X  | X  | X  | X  | X  | X  | X               | X                   | X               | X               | X               | X  | X  | X               |
| Alpha-2 macro globulin, Haptoglobin, Apolipoprotein A1                           | X                    |                                   |       |   |   |   |   |   |    |    |    |    |    |    |                 |                     |                 |                 |                 |    |    |                 |
| Viral sequencing                                                                 | X                    | X                                 | X     | X | X | X | X | X | X  | X  | X  | X  | X  | X  | X               | X                   | X               | X               | X               |    |    | X               |

## HBsAg loss during treatment with Peg-IFN combined with ADV or TDF

|                                         |   |   |   |   |   |   |   |   |   |   |   |   |   |   |   |   |   |   |   |   |   |   |
|-----------------------------------------|---|---|---|---|---|---|---|---|---|---|---|---|---|---|---|---|---|---|---|---|---|---|
| PBMC's (frozen for central processing)  | X | X | X | X |   | X |   | X | X |   | X |   | X |   | X | X |   |   |   |   |   | X |
| PAXgene™ DNA (j) (human genomics)       |   | X |   |   |   |   |   |   |   |   |   |   |   |   |   |   |   |   |   |   |   |   |
| PAXgene™ RNA (k) (human genomics)       |   | X |   |   |   | X |   |   | X |   |   |   |   |   | X | X |   |   |   |   |   | X |
| Plasma tube (proteomics profiling ) (l) |   | X |   |   |   | X |   |   | X |   |   |   |   |   | X | X |   |   |   |   |   | X |
| Adverse events                          |   | X | X | X | X | X | X | X | X | X | X | X | X | X | X | X | X | X | X | X | X | X |
| Quality of life (m)                     |   | X |   |   |   |   |   |   | X |   |   |   |   |   | X |   | X |   |   |   |   | X |
|                                         |   |   |   |   |   |   |   |   |   |   |   |   |   |   |   |   |   |   |   |   |   |   |

Chemistry 1 : ASAT, ALAT,

Chemistry 2: sodium, chloride, potassium, bilirubin, creatinine, urea, prothrombin time, APTT, antitrombine III, alkaline phosphatase, calcium, phosphorus, total protein, albumin, uric acid, TSH, free T4 and glucose.

Chemistry 3: cholesterol, triglycerides, sober glucose

B: baseline

- (a) For females of child bearing potential only, a pregnancy test will be performed within 24 hours prior to first dose. A pregnancy test must be done at any time a secondary amenorrhea of more than 1 week occurs.
- (b) Only for patients with pre-existing pulmonary disease (Not necessary if (1) a chest X-ray available to the investigator has been obtained within the past 12 months and (2) the patient's pulmonary disease has been clinically stable)
- (c) Patients with cirrhosis or marked fibrosis on liver biopsy or raised AFP need to have a liver imaging study during the screening period to rule out hepatic neoplasia.
- (d) For anyone with preexisting cardiac disease.
- (e) Eye examination will be done on indication. Any patient complaining of decrease or loss of vision must have a prompt and complete eye examination. Patients with preexisting ophthalmologic disorders (eg, diabetic or hypertensive retinopathy) should receive periodic ophthalmologic exams during Peg-IFN therapy. Peg-IFN treatment should be discontinued in patients who develop new or worsening ophthalmologic disorders.
- (f) non-invasive measurement of the liver to detect fibrosis and cirrhosis
- (g) Only for patients with decreased kidney function. If there are clinically significant laboratory abnormalities, repeat no less frequently than every 2 weeks or as clinically indicated, with appropriate toxicity management, until they return to normal or baseline values. Urinalysis to be performed via dipstick, with subsequent microscopic evaluation if positive for hemoglobin at the discretion of the investigator.
- (h) Only for certain patients at risk, don't repeat if data from previous assessments are available
- (i) Roche TaqMan®; when HBV DNA is more than the maximal detection limit, ten or hundred time dilution is proceeded.
- (j) Paxgene TM DNA sample (tube) will be collected. The DNA samples will be used exclusively for exploratory DNA research (genotyping of hostgenomics) to evaluate drug disposition genes.(e.g. metabolic enzymes and drug transporters), to explore possible underlying genetic variants involved in therapy response in HBV chronically infected. Samples will only be processed in a number of subjects. No other testing will be performed on these samples.
- (k) Paxgene TM RNA sample (tube) will be collected to assess the expression of RNA in peripheral blood using whole genome microarray technology. These samples are collected as part of an effort to better understand the effects of medication. Samples will only be processed in a number of subjects. No other testing will be performed on these samples.
- (l) plasma tube will be collected for proteomics profiling. These samples are collected as part of a study to better understand the effects of medication on liver activity. Samples will only be processed in a number of subjects. No other testing will be performed on these samples. Possible protein candidates include: SR-B1(CD36), CD81, certain Claudins, STAT-1 and 2, ApoE and more.
- (m) During the study a quality of life index according to SF36 standardized questionnaires will be administered

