#### Dosages, dosage modifications and method of administration

##### Hematological:

Dose reduction from 180µg to 135µg is required if absolute neutrophil counts are < 750/mm^3. If ANC < 500/mm^3, treatment should be suspended until ANC values return to more than 1000/mm^3. Treatment must be reinstituted at 90 µg and monitor ANC needs to be monitored. When platelet counts are < 50,000/mm^3, dosage must be reduced to 90 µg. Treatment must be discontinued if platelet count < 25,000/mm^3.

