### Liver Function

If ALT increases are progressive despite dose reduction or accompanied by increased bilirubin or evidence of hepatic decompensation, therapy should be immediately discontinued.

In chronic hepatitis C patients with progressive ALT increases above baseline values, the dose of PEGASYS should be reduced to 135 µg and more frequent monitoring of liver function should be performed. After PEGASYS dose reduction or withholding, therapy can be resumed after ALT flares subside.

In chronic hepatitis B patients with elevations in ALT ( $> 5 \times \text{ULN}$ ), more frequent monitoring of liver function should be performed and consideration should be given to either reducing the dose of PEGASYS to 135 µg or temporarily discontinuing treatment. After PEGASYS dose reduction or withholding, therapy can be resumed after ALT flares subside.

In patients with persistent, severe (ALT  $> 10$  times above the upper limit of normal) hepatitis B flares, consideration should be given to discontinuation of treatment. (35).

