### **7.3. Study procedures**

Study procedures are listed in table 2.

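### As printed, footnote (g) of Table 2 limits haematology and Chemistry 1 and 2 to patients with decreased kidney function, against the dosing, monitoring and eligibility text: a minor drafting error in the safety schedule

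*Protocol*

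**What the plan says.** Section 7.3 of the protocol consists of one instruction: "Study procedures are listed in table 2". In Table 2 of the Appendix, marker (g) appears on four rows: "Complete hematology with differential WBC, and platelets", Chemistry 1, Chemistry 2 and the urine dipstick. The notes under the table define Chemistry 1 as ASAT and ALAT. They define the second panel as "Chemistry 2: sodium, chloride, potassium, bilirubin, creatinine, urea, prothrombin time" and further items.

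Footnote (g) has three parts. It opens "Only for patients with decreased kidney function", then gives a rule for repeating abnormal laboratory tests, then gives handling instructions for the dipstick. Nothing ties the opening restriction to one row.

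The long-term follow-up table uses (g) again on haematology, Chemistry 1 and Chemistry 2.

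**The concern.** Other footnotes in the same list use the same kind of opening to restrict the row they mark: (b) for the chest X-ray and (h) for the autoantibodies. Read in the same way, (g) confines blood counts, transaminases, bilirubin and creatinine to patients with decreased kidney function. Few such patients can be in the trial, because exclusions 1 and 13 remove significant renal disease and creatinine above 1.5 times the upper limit of normal.

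The tests concerned drive dose changes. In section 6.2 the protocol reports that 40% of hepatitis B patients on Peg-IFN needed a dose modification, most often for laboratory abnormalities (neutropenia 20%, thrombocytopenia 13%, ALT disorders 11%). Section 8.1 gives visit weeks and refers to laboratory tests in general. Table 2 alone assigns each blood panel to particular on-treatment visits, and the restriction is printed there. A site ordering tests strictly from the schedule would have a printed reason to leave them out.

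**Working it through.** No calculation underlies this point. The check sets the footnote beside the text that depends on the same tests.

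| Row under (g) | Text that needs the result | Limited to renal patients there? |
|---|---|---|
| Haematology | Section 6.2, PEGASYS, Hematological. Below 500/mm³ neutrophils, "treatment should be suspended until ANC values return to more than" 1000/mm³. "Treatment must be discontinued if platelet count" is below 25,000/mm³. | No |
| Haematology | Section 4.3, exclusions 11 and 12 (neutrophils, platelets, haemoglobin at screening) | No |
| Chemistry 1 | Section 6.2, PEGASYS, Liver Function: action on ALT above 5 times and above 10 times ULN | No |
| Chemistry 1 | Section 4.2, inclusion 6: two ALT values, at least one of them in the screening period | No |
| Chemistry 2 (bilirubin) | Section 6.2, PEGASYS, Liver Function: if ALT rises are "accompanied by increased bilirubin or evidence of hepatic decompensation, therapy should be immediately discontinued" | No |
| Chemistry 2 (bilirubin, creatinine) | Section 4.3, exclusions 7 and 13 | No |
| Chemistry 2 (creatinine) | Section 6.2, adefovir, risks and dosage: renal monitoring in every patient | No |
| Chemistry 2 (creatinine) | Section 6.2, tenofovir, risks: creatinine clearance in every patient before starting | No |
| Haematology and chemistry | Table 3, screening | No |

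**Reach by arm.** The Peg-IFN rules apply to both treated groups, planned as 50 + 50 = 100 patients. The adefovir monitoring text applies to one group of 50. For tenofovir the conflict is confined to the pre-treatment value, because routine renal monitoring during treatment is advised only for patients at risk or with mild impairment. For the untreated controls, the conflict is with eligibility and Table 3 only.

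**What was intended.** Section 8.1 sets safety assessments at screening, baseline, weeks 1, 2, 4, 6, 8 and 12, every 6 weeks to week 48, and weeks 50, 52, 56, 60 and 72. It counts laboratory tests among the safety measures and sets no renal condition. That makes 2 (screening, baseline) + 6 (weeks 1 to 12) + 6 (weeks 18, 24, 30, 36, 42, 48) + 5 (weeks 50, 52, 56, 60, 72) = 19 visits. The haematology row of Table 2 has 20 X marks: those 19 visits and day 3. The row was evidently built as a schedule for all patients.

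**Where the sentence probably belongs.** Footnote (g) ends with dipstick instructions, and the urinalysis row is already labelled as done on indication. A renal restriction reads naturally there and nowhere else. No text in the protocol says so, however.

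**Endpoint.** The HBsAg row does not carry (g), so the primary endpoint is untouched.

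**The case against.** The strongest reply is that nobody would misread this. Section 8.1 already schedules laboratory safety assessments for all patients, Table 3 covers screening without a renal condition, and the dose rules make no sense without the tests. The marker letters in these tables are also loose elsewhere. HBV-DNA carries (i), the assay note, in Table 2 but (h), a note on patients at risk, in the long-term table. A superscript (a), the pregnancy-test note, sits on several week headings. All of this stands, and it is why the point is minor. It does not remove the printed conflict: section 8.1 names no panels and Table 3 ends at screening.

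Four stronger readings are tempting but are not supported.

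- A reader might count the X marks on the three blood-test rows (20 + 18 + 9 = 47 per patient) as tests that would be lost. They are only marks under a misworded footnote, and the rest of the protocol points to their being done.
- A reader might call the condition circular, since creatinine is itself in Chemistry 2. Table 3 lists creatinine for screening without restriction, so impaired patients can be identified at entry. Circularity remains only for impairment that develops later.
- A reader might see the same conflict in the long-term table. Those yearly visits come after treatment, haematology and Chemistry 2 have no X there and are on indication, and none of the texts set out above requires yearly ASAT or ALAT.
- A reader might see a contradiction between the 2-week repeat interval in (g) and the 4-week one in section 8.1. Section 8.1 sets a minimum frequency and allows shorter intervals, so repeating every 2 weeks satisfies both.

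**Conclusion.** The conflict is real as printed. Three blood-test rows of Table 2 carry a restriction that the dosing, adefovir and tenofovir monitoring, eligibility and Table 3 texts contradict, and nothing in the protocol confines it to urinalysis. It is a minor drafting error in an operative safety schedule, because section 8.1 and the X marks show that all patients were to be tested. The documents do not show that any test would be omitted, and they show no effect on the efficacy analysis.

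The conclusion assumes that the markers are printed as the extracted text shows them. The letter (g) recurs on four rows of Table 2 and three of the long-term table, and its wording is a complete sentence, so an extraction fault is unlikely. That the sentence was meant for urinalysis is an inference from the rest of the footnote.

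**What to change.** Remove the kidney-function sentence from the haematology, Chemistry 1 and Chemistry 2 rows of Table 2. Leave the rule on repeating abnormal tests on those rows. If the restriction is wanted for the dipstick, give it a separate marker on the urinalysis row and apply it only after screening, because Table 3 lists the screening dipstick without restriction. As housekeeping, relabel the long-term table, which reuses (g), so that it matches. Haematology and Chemistry 2 there keep their on-indication label.

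The cost is one footnote split by amendment. No scheduled test or visit is added, and sample size and analysis do not change.
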